### Outcome measures and endpoints

The CGM is specifically designed for use in intensive care medicine. However, for it to be successfully implemented in clinical use and to confirm the advantages of continuous assessment of blood glucose levels in this setting, the clinical workflow must be accounted for. At the University Hospital Heidelberg (Interdisciplinary Operative Intensive Care Unit), blood samples are collected for point-of-care blood gas analyses using a BGA, and blood glucose levels are assessed as a by-product every hour. Nurses change shift every 8 h.

In this setting, the BGA is established as the standard device, and is used instead of the larger devices used in certified central laboratories. Nevertheless, we will also independently compare the results from the point-of-care BGA with those determined by a central laboratory-based device. The level of agreement between values measured by the CGM and a BGA will be assessed ≥ 8 h after the initial placement and calibration of the CGM.

### Primary outcome measure

The primary outcome measure, referred to as the agreement at point of care, is defined as the level of agreement in blood glucose levels determined by the CGM and a BGA, assessed 8 h after the initial placement and calibration of the CGM.

The agreement for the *i*th patient will be quantified as the relative difference $d_{i}$ between readings ($y_{\mathrm{gi}}$) and measurement results ($y_{\mathrm{ri}}$), calculated as $d_{i}=\frac{2\left(y_{\mathrm{gi}}-y_{\mathrm{ri}}\right)}{y_{\mathrm{gi}}+y_{\mathrm{ri}}}$. Using the approach suggested by Bland and Altman [9,10] the limits of this agreement are set to $\bar{d}\pm 2s_{d}$, where $\bar{d}$ and $s_{d}$ are the empirical mean and the standard deviation of *d*_*i*_.

According to the guidelines for quality assurance in quantitative laboratory tests issued by the German Medical Association (GMA) [11,12], the measurement results from any device should not differ from an established standard by more than 15%. In this setting, however, the standard is not an unknown clinical value measured with a standard device but instead a prepared sample for which accuracy was achieved by titration or other methods. Unlike this method, the test–retest variance of the standard device contributes to the total error in our study. Moreover, the asymmetrical measure $\frac{1}{y_{0}}\sqrt{\frac{1}{n}{\left(y_{i}-\;y_{0}\right)}^{2}}$ is smaller than the measure $\left|\bar{d}\right|\pm 2s$ taken from the symmetrical limits of agreement under any but highly unlikely conditions. Thus $\bar{d}\pm 2s_{d}$ has been set to 20%, which is more conservative than the requirements imposed by the GMA. Therefore, the agreement at point-of-care is considered sufficient if the limits of agreement of the relative difference and their 95% confidence intervals (CIs) are within 20%.

### Secondary outcome measures and endpoints

Secondary outcomes include the following:

• Deteriorations in agreement between the CGM and BGA values measured in the short (1 and 2 h) and medium term (3–8 h) after initial placement and calibration of the CGM

• Agreement beyond point of care, defined as the agreement in blood glucose levels determined by the CGM and a BGA, recorded at 9 and 10 h after the initial placement and calibration of the CGM

• Long term deterioration in agreement measured at 16 and 24 h after initial placement and calibration of the CGM

• Rate of unwanted effects and events defined in DIN EN ISO 14155 2012–01 [Clinical investigation of medical devices for human subjects – Good clinical practice (ISO 14155:2011 + Cor. 1:2011)].

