**Patients meeting all of the following criteria will be considered for admission to the study:**
· Undergoing major abdominal surgery, predominantly pancreatic surgery (pancreatectomy), for any reason
· Require careful postoperative monitoring of blood glucose levels
· Expected to be under intensive care for ≥ 8 h after surgery
· Insertion of a multi-lumen central venous catheter for medical reasons (e.g., anaesthesia and operative purposes)
· Aged 18–80 years
· Able to understand the design and possible consequences of the clinical study
In addition, all patients must meet the following criteria, or will not be included in the study:
· Successful central venous cannulisations with a multi-lumen catheter
· One lumen is not needed for medical purposes, such as perioperative fluid therapy or medication administration
Patients fulfilling any of the following criteria will be excluded from the study:
· History of thrombosis, embolism, or vascular obliteration
· Bleeding disorders (e.g., thrombocytosis)
· Acute or chronic cardiac failure
· Acute or chronic kidney failure (i.e., patients on renal replacement therapy)
· Evidence of postoperative hyperhydration (pulmonary vascular congestion)
· Acquired immune deficiency syndrome
· Receiving immunosuppressive therapy
· Signs or symptoms of acute or chronic infection
· No perioperative antibiotic prophylaxis (with mezlocillin 4 g and metronidazole 500 mg, for example)
· No perioperative prophylaxis to prevent venous thromboembolism (e.g., unfractionated or fractioned/low-molecular weight heparin)
· The amount of flushing medium administered is > 500 mL
· Pregnancy or lactation
· Participation in other clinical studies and observation period of competing studies, respectively

No patient will be allowed to enrol in this study more than once.

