### Measurement process

All subjects will first enter a screening stage lasting up to 1 month, and an additional 2-h reference period before the study period. The study will consist of a 24-h measurement period and a 48-h follow-up period. During the measurement period, blood samples will be obtained 13 times. The overall duration of the measurement stage will be determined by the duration of intensive care.

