### Statistical methods

The test statistic for testing the null hypothesis $H_{o}:\left|\delta \right|+2\sigma >\lambda$ is calculated as $Z=\frac{\left|\bar{d}\right|\pm 2s_{d}-\lambda }{\sqrt{3/ns_{d}^{2}}}$, where λ=20% for the outcome measure. Its distribution under $\left|\delta \right|+2\sigma =\lambda$ is asymptotically normal. Therefore, the null hypothesis is rejected if *Z* is below the 0.05 quantile of the normal distribution. Descriptive statistics of continuous variables and scores include the number of observations, the mean and standard deviation, the median, minimum, and maximum. Descriptive statistics of categorical variables (nominal or ordinal) include absolute and relative frequencies (n and per cent). The primary outcome measure is the level of agreement in blood glucose levels determined by the CGM and a BGA, assessed 8 h after the initial placement and calibration of the CGM using the relative difference $\bar{d}$, as described above. Bland and Altman plots will be drawn, including the CIs for the mean difference and limits of agreement to show the agreement between the pairs of values [9,21]. Secondary analyses, including the level of agreement between the two devices at each time after placement and calibration of the CGM will be analysed descriptively, while applying the same equivalence bounds used in the primary analysis. A linear mixed model will be developed using time as the fixed factor. Subject and the interaction subject × time will be included as random explanatory variables. The individual values $\bar{d}$ at all times up to 8 h will be included as the response variable. This model will be used to impute missing data. Biometric analysis will be defined in the statistical analysis plan, which must be authorised before the database is opened by the biostatistician, the sponsor, and the principal investigator.

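### If length of stay is related to agreement, the 16-h and 24-h results mix patient selection, and the 8-h recalibration, with sensor drift

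*Protocol article*

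**What the plan says.** Drift and shift are part of the study objective (Objectives). The matching late endpoint is "Long term deterioration in agreement measured at 16 and 24 h after initial placement and calibration of the CGM" (Secondary outcome measures and endpoints).

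For the analysis, Statistical methods states: "Secondary analyses, including the level of agreement between the two devices at each time after placement and calibration of the CGM will be analysed descriptively", and adds "while applying the same equivalence bounds used in the primary analysis". The same section describes a linear mixed model with time as fixed factor and with subject and subject × time as random terms. Its data are limited: the relative differences "at all times up to 8 h will be included as the response variable". Of that model it says "This model will be used to impute missing data".

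Three provisions determine who is measured late:

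- Table 1 requires a patient to be "Expected to be under intensive care for ≥ 8 h after surgery".
- Measurement process says: "The overall duration of the measurement stage will be determined by the duration of intensive care".
- Study period (Visits 2–14) says that on discharge before 24 h the 24-h visit (Visit 14) is moved forward and the device is taken out.

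The same section and Table 2 have the device recalibrated at 8 h, with later readings at 9, 10, 16 and 24 h.

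**The concern.** Deterioration is a change over time, and drift is a change within one sensor in one patient. The protocol models within-patient change up to 8 h, the period that every eligible patient is expected to complete. It states no such analysis for the period in which patients may leave.

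A reader who follows the text has one set of limits at 8 h and another at 16 or 24 h, the later ones possibly from fewer and different patients. If those who remain agree with the blood gas analyser better or worse than those who left, the limits move although no sensor has changed. A stable device could seem to deteriorate, or a drifting one could seem stable. The result is also read against the 20% bound, so selection could change whether the device appears acceptable at 24 h.

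The comparison has a second defect. The 8-h reading is taken 8 h after the initial calibration. The 16-h and 24-h readings come 8 h and 16 h after a recalibration, although the endpoint counts time from the initial calibration. Even a fixed group of patients would not show uninterrupted drift since placement.

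**Working it through.** **The protocol's own figures.** Sample size gives the standard error of a limit of agreement as √(3s²/n).

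- CI half-width at n = 100: 1.96 × √(3/100) = 0.339 s, matching the stated 0.34 s.
- Threshold: 1.645 + 0.842 ≈ 2.486, as stated.
- With mean 5%, SD 6% and n = 100: Z = (5 + 12 − 20)/√(3 × 36/100) = −2.887. Power = Φ(2.887 − 1.645) = 89.3%, consistent with the stated value above 80%.

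These figures concern the primary 8-h test and are sound.

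**Effect of selection with no drift.** The document gives neither the share still measured at 24 h nor agreement by length of stay, so both are assumed. Let p be the share staying, with SDs of the relative difference s_S in stayers and s_L in leavers, and mean difference zero in both.

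- Limits at 8 h, all patients: ±2√(p·s_S² + (1 − p)·s_L²)
- Limits at 24 h, stayers only: ±2·s_S

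| p | SD stayers / leavers | 8-h limits | 24-h limits | Apparent change (points) |
|---|---|---|---|---|
| 40% | 8% / 5% | 2√40.6 = 12.7% | 16.0% | +3.3 |
| 80% | 8% / 5% | 2√56.2 = 15.0% | 16.0% | +1.0 |
| 90% | 8% / 5% | 2√60.1 = 15.5% | 16.0% | +0.5 |
| 40% | 5% / 8% | 2√48.4 = 13.9% | 10.0% | −3.9 |
| 80% | 5% / 8% | 2√32.8 = 11.5% | 10.0% | −1.5 |
| 90% | 5% / 8% | 2√28.9 = 10.8% | 10.0% | −0.8 |
| any | equal | same | same | 0 |

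**Against the 20% bound.** Take the first row with 100 patients at 8 h and 40 at 24 h.

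- 8 h: 12.7 + 1.96 × √(3/100) × 6.37 = 14.9%
- 24 h: 16.0 + 1.96 × √(3/40) × 8 = 16.0 + 4.3 = 20.3%

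The bound is met at 8 h and missed at 24 h with no drift.

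**At the protocol's planning values.** Hold the 8-h group at mean 5% and SD 6%: upper limit 17.0%, upper confidence bound 19.0%. Suppose half leave (mean 3%, SD 5%) and half stay (mean 7%, SD 6.24%). The pooled variance is 0.5 × 25 + 0.5 × 39 + 4 = 36, as required.

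- Upper limit among the 50 stayers: 7 + 2 × 6.24 = 19.5%
- Upper confidence bound: 19.5 + 1.96 × 6.24 × √(3/50) = 22.5%

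The apparent worsening is 2.5 points. In 2,000 simulated trials it averaged 2.4 points, and −0.03 when the same stayers were compared at both times. Over the scenarios tried, with 25% to 75% staying, the 24-h upper limit ran from 15.9% to 23.0% with no drift.

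**Loss of numbers alone.** With mean 5% and SD 6% unchanged, the upper confidence bound 17 + 1.96 × 6 × √(3/n) is 19.4%, 19.9% and 20.7% for n = 75, 50 and 30. At 30 pairs the bound is crossed without drift or selection.

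**The case against.** The strongest reply is that the protocol never says deterioration will be read as the 24-h limits minus the 8-h limits in whoever remains. A reader might infer this, but the text names only the endpoint and a descriptive analysis at each time. It defines no analysis set and does not exclude paired changes. It also leaves the detailed analysis to a statistical analysis plan that is not shown. All of this stands. What remains is that the one analysis stated for these times cannot separate selection from drift, and that the one stated within-patient model is explicitly limited to 8 h.

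A reader might also assume that patients who stay longer are sicker, with less stable glucose. No passage says so or links stay to agreement, and Table 1 excludes cardiac failure, kidney failure, infection and hyperhydration, which narrows the case mix. On the other side, the Participants section recruits a mixture of surgical procedures to widen the glucose range, so a link with stay is possible. Its direction is unknown.

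Size is a fair objection too. The protocol treats discharge before 24 h as a contingency, so the share staying may be high, and at 80% to 90% the artefact is only 0.5 to 1.5 points. At 40% of 100 patients the CI half-width of the 24-h limit, 4.3 points, exceeds the apparent change of 3.3. The planned plots with confidence intervals would show that imprecision, but they would not remove the bias.

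**Conclusion.** The point holds conditionally. The stated analysis of agreement at 16 and 24 h cannot distinguish a change in the sensor from a change in who is measured, and any comparison with 8 h also crosses a recalibration.

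Under assumed SDs of 8% and 5%, the false change in the limits is 3.3 to 3.9 points if 40% stay and 0.5 to 1.5 points if 80% to 90% stay, in either direction. It is zero if stay is unrelated to agreement. The shares and SDs are illustrations, and the document supports no estimate of the actual bias.

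It would go too far to conclude that the late results will be biased or that they will overstate deterioration. The endpoint is secondary and descriptive. The primary 8-h conclusion, the sample size and the interim rule are untouched. It still deserves correction, because drift is a stated objective and the readings needed are already scheduled.

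**What to change.** Define deterioration at 16 and 24 h as within-patient change among patients measured at both times, against the same patient's 9-h and 10-h readings. State that this measures drift since the 8-h recalibration, not since the initial calibration, and align the endpoint wording with that. Alternatively, extend the mixed model to 24 h with a recalibration term and the actual time since calibration.

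In either case:

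- report the mean and SD of the change, and the limits of agreement at both times in that same set of patients;
- give the number measured at each time;
- analyse brought-forward Visit 14 readings at their actual time, not as 24-h values;
- keep the limits in all available patients as supporting data.

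The cost is wording and a further analysis, with no new sampling. The paired set is smaller and its confidence intervals wider: at 40 pairs the half-width of a limit is 1.96 × √(3/40) = 0.54 s, against 0.34 s at 100. The paired result also describes only patients who stay, which the report should say.

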### Sample size

The agreement between the two devices will be quantified using the approach suggested by Bland and Altman, in which the 95% limits of agreement with 95% CIs will be compared with a prespecified, clinically acceptable relative difference [9] of 20%. The standard error of the 95% limits of agreement is approximately $\mathrm{se}\approx \sqrt{\frac{3s_{d}^{2}}{n}}$, where $s_{d}$ is the standard deviation of the differences between the two devices and n is the sample size (number of paired values the differences are calculated from). The sample size is dependent on the intended width of the CIs. Bland and Altman recommend a sample size of 100, which gives a 95% CI of about ± 0.34$s_{d}$, or about one-sixth of the width of the actual agreement. The power to reject the hypothesis that the prespecified limits of agreement of ± 20% are violated is > 80% if $\frac{\delta +\;2\sigma -\;\lambda }{\sqrt{\frac{3\sigma^{2}}{n}}}<-\;2.486$, where λ is the 20% limit and *δ* and $\sigma^{2}$ represent the expected value and variance of *d*, respectively. This inequality may be approximated by δ+2.5σ<λ indicating that the power is sufficient with *δ* = 5% and *σ* = 6%, for example. To fulfil the sample size recommended by Bland and Altman (i.e., ≥ 100 pairs of values), we plan to enrol up to 130 patients in this study.

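### The general condition for more than 80% power covers the upper limit of agreement only, so power is about 67% on its boundary at zero bias and the condition fails for negative bias

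*Protocol article*

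**What the plan says.** The criterion is two-sided. Under Primary outcome measure, agreement at point of care is sufficient if "the limits of agreement of the relative difference and their 95% confidence intervals (CIs) are within 20" per cent. Both the upper and the lower limit must therefore pass.

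The test follows the criterion. Under Statistical methods, the null hypothesis is |δ| + 2σ > λ with λ = 20%. The statistic Z compares |d̄| and 2s_d with λ, in units of √(3s_d²/n), and the null is rejected if Z "is below the 0.05 quantile of the normal distribution". The interim analysis section writes the same statistic with |d̄| + 2s_d, which is the worse of the two limits.

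The power statement does not follow it. Under Sample size, "The power to reject the hypothesis that the prespecified limits of agreement of" ±20% are violated exceeds 80% if (δ + 2σ − λ)/√(3σ²/n) < −2.486, where δ carries its sign. This is then approximated by δ + 2.5σ < λ, with δ = 5% and σ = 6% as the example. The number of patients rests on a recommendation of at least 100 pairs, with up to 130 patients enrolled.

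**The concern.** A power condition should describe the test that will be run. Here the test takes the worse of two limits, while the condition describes one. The difference shows in two places.

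- **Bias near zero.** Both limits then lie about equally close to ±20%, and either can fail by chance. The probability that both pass is lower than the probability that one passes.
- **Negative bias** (the monitor reads below the analyser). The lower limit is then the critical one. The signed condition becomes easier to meet as the true agreement gets worse.

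At stake is whether a reader can use the condition to see which combinations of bias and spread the study can confirm with more than 80% power.

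**Working it through.** **Inputs.** λ = 20%; n = 100 pairs, with 130 as the upper bound (Sample size); one-sided 0.05, critical value 1.645 (Statistical methods); standard error of a limit √(3σ²/n) (Sample size). The ± in the printed Z is read as +, in line with the null hypothesis and the interim statistic.

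**1. The protocol's constant.** u(0.95) + u(0.80) = 1.645 + 0.842 = 2.487, which agrees with the printed 2.486 up to rounding (1.6449 + 0.8416 = 2.4865). This is the constant for a one-sided 5% test of one limit with 80% power: Φ(2.486 − 1.645) = Φ(0.841) = 0.80.

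**2. The boundary.** Setting the condition to equality gives σ = (20 − δ)/(2 + 2.486·√(3/n)).
- n = 100: √0.03 = 0.1732. At δ = 0, σ = 20/2.4306 = 8.23%.
- n = 130: √(3/130) = 0.1519. At δ = 0, σ = 20/2.3777 = 8.41%.

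**3. Both limits, asymptotically.** The estimated limits are d̄ + 2s and, mirrored, −d̄ + 2s. Var(d̄) = σ²/n and Var(2s) ≈ 2σ²/n, so their correlation is (2 − 1)/3 = 1/3. At δ = 0 each limit has margin 0.841. The bivariate normal probability that both pass is 0.669.

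**4. Both limits, by simulation.** Draw d̄ ~ N(δ, σ²/n) and s² ~ σ²χ²(n−1)/(n−1). Success is |d̄| + (2 + 1.645·√(3/n))·s < 20. On the boundary with n = 100:

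| δ | σ | upper limit only | both limits |
|---|---|---|---|
| 0 | 8.23% | 78.7% | 66.6% |
| 0.25% | 8.13% | 78.7% | 71.9% |
| 0.5% | 8.02% | 78.7% | 75.3% |
| 1% | 7.82% | 78.7% | 78.1% |
| 5% | 6.17% | 78.7% | 78.7% |

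The gap between the two columns is the two-limit effect: 12 points at zero bias and under 1 point at δ = 1%. The remaining distance from 78.7% to 80% comes from the normal approximation and is a different matter. At n = 130 the boundary at δ = 0 (σ = 8.41%) again gives 66.6%, so a larger n does not repair the condition.

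**5. Negative bias.** Take δ = −5%, σ = 9%, n = 100. The condition gives (−5 + 18 − 20)/(9 × 0.1732) = −7/1.559 = −4.49, well below −2.486. Yet |δ| + 2σ = 5 + 18 = 23% > 20%, so the null hypothesis is true. The simulated probability of rejecting it is about 0.05%.

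**6. The protocol's shortcut and example, n = 100.**
- Shortcut edge at zero bias (σ = 8%): (16 − 20)/(8 × 0.1732) = −2.89. Power for both limits is about 79% under the 0.05 rule.
- Worked example (5%, 6%): (5 + 12 − 20)/(6 × 0.1732) = −2.89. Power is about 88% under the 0.05 rule. It is 80.5% if success needs the two-sided 95% confidence intervals inside ±20% (1.96 in place of 1.645).

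**7. Largest σ for 80% joint power, n = 100.**

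| Rule | δ = 0 | δ = 5% |
|---|---|---|
| one-sided 0.05 | 7.99% | 6.15% |
| 95% CI | 7.81% | 6.01% |
| stated −2.486 condition | 8.23% | 6.17% |

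**The case against.** The strongest reply is that 67% belongs to one point: zero bias, exactly on the edge of a strict inequality. The protocol does not plan on that point. Its working rule is the shortcut, whose slack (2.5 in place of 2.43) brings power at zero bias to about 79%, and its only worked assumption keeps more than 80% under either decision rule. The sample size rests on the 100-pair recommendation, not on this condition. In terms of σ the error at zero bias is 8.23% against 7.99%. All of this stands and limits the consequence. It does not make the general statement true, and it leaves the sign of δ unanswered: the shortcut, too, is met by δ = −5%, σ = 9%, since −5 + 22.5 = 17.5 < 20.

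Three stronger readings are tempting, and the protocol does not support them.

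- **That the study has only 67% power for a device with little bias.** The shortfall is already under 1 point at δ = 1%. For a fixed σ, power rises as bias falls; at δ = 0 with the example's σ of 6% it is practically 100%. The 67% arises only because the boundary lets σ grow to 8.23%.
- **That the 78–79% at larger bias is the same error.** The upper limit alone gives 78.7% there too.
- **That power is lower still, about 55% at the zero-bias boundary, under the 95% confidence interval rule.** That figure also contains a separate issue: the Primary outcome measure section speaks of 95% intervals, while Statistical methods uses a one-sided 0.05 quantile. It should not be charged to the one-limit formula.

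**Conclusion.** The point holds for the general condition in the Sample size section. As written, it promises more than 80% power from a signed, one-limit formula, while the criterion and the test need both limits. On its boundary the joint power is about 67% at exactly zero bias, at n = 100 and n = 130 alike, and it recovers to the one-limit value once bias exceeds about 1%. With negative δ the condition can be met when the null hypothesis is true.

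The figures assume normally distributed relative differences, one pair per patient, all n pairs analysed and the one-sided 0.05 rule, unless stated otherwise. Neither the worked example nor the planned 100 to 130 patients is shown to be underpowered. This is a false statement that should be corrected; it is not a fault in the size of the study.

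**What to change.** In the Sample size section, write |δ| in place of δ, in the condition and in the shortcut. Replace the −2.486 statement with the joint power for both limits at stated δ and σ, by simulation or bivariate integration, for the decision rule that is finally used. The σ limits in step 7 of the working can be quoted directly, and the worked example can stay with its joint power given beside it.

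The cost is a text correction and a short calculation. Sample size, visits and conduct stay as they are.
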